## Abstract

**Supplementary Information:**

The online version contains supplementary material available at 10.1186/s12883-023-03344-x.

## Introduction

X-linked dystonia-parkinsonism (XDP) is an uncommon and progressive neurodegenerative movement disorder which presents with adult-onset parkinsonism and dystonia [1]. It is also found almost exclusively in males from Panay Island in the Philippines and all the cases described so far have been linked to Filipino ancestry [1]. XDP is linked to mutations in the DYT3/TAF1 gene [2]. The prevalence of XDP globally is 5.74 per 100,000 individuals in Panay Island and 0.31 per 100,000 in the Philippines [1]. The majority of patients (95%) are males, and the mean age of onset is 39–40 years [1, 3]. Furthermore, the mean duration of illness is approximately 16 years and the mean age of death is approximately 55.6 years [1].

XDP is characterized by focal dystonic movements affecting the upper and lower extremities, the craniofacial area, and neck and shoulders, before becoming generalized within two to five years [1]. In some cases, parkinsonism may present initially [3]. Dystonia may co-exist or is replaced by parkinsonism usually beyond the tenth year of illness, manifesting as tremors and other symptoms, such as bradykinesia and gait instability [1]. As a result, patients have decreased life expectancy and poor quality of life [1, 4].

Pharmacologic treatment includes oral medications (carbidopa/levodopa, trihexyphenidyl, biperiden, haloperidol, diazepam, zolpidem, milacemide, anticonvulsants, and antihistamines). However, the response rate is variable and, in several cases, suboptimal [5, 6]. Chemodenervation using botulinum toxin A and muscle afferent blockade have been also been utilized [7, 8].

Historically, the first surgical treatment for XDP, ablative surgeries, was performed at the Philippine General Hospital (PGH) in 1960 when the Filipino neurosurgeon, [name], treated two brothers with bilateral chemopallidectomies [9]. This was followed by other lesioning procedures (e.g., bilateral cryothalamotomy, bilateral thalamotomy, ventrocaudal nucleus, unilateral cryothalamotomy, and bilateral thalamotomy followed by a cerebellar stimulation device implantation) performed in 6 more patients between 1966 and 2002 in various treatment centers abroad [9]. However, the generally poor surgical outcomes and high morbidities from these early ablative procedures discouraged further surgical procedures for XDP until the advent of deep brain stimulation (DBS) surgery [9]. Since 2006, DBS surgery has been shown to be immediately effective and robust in alleviating the debilitating symptoms of XDP [10, 11]. However, DBS surgery is a very expensive procedure and continues to be unaffordable for most XDP patients [12, 13].

Due to the prohibitive cost of DBS procedures, there had been a revival of ablative or lesioning surgeries for movement disorders like dystonia, essential tremor (ET), and Parkinson’s disease (PD) [14]. One of the most recent technologies introduced for brain lesioning is high intensity focused ultrasound or transcranial magnetic resonance-guided focused ultrasound (MRgFUS), with the pallidothalamic tract (PTT) as the target for treating XDP-related symptoms [15, 16]. Pallidothalamic tractotomy, or campotomy, was until recently considered an abandoned lesioning procedure that was previously used in the treatment of various extrapyramidal disorders [17]. However, it was revived in 2005 to treat PD with the idea that targeting the PTT (H1 field of Forel) in the area where the pallidothalamic fibers of the fasciculus lenticularis (H2 field of Forel) and ansa lenticularis converge on their way to the ventroanterior and ventrolateral nuclei of the thalamus would combine the advantages of a thalamotomy and pallidotomy [17]. The PTT is a small area measuring around 4 mm in diameter and is located just medial to the mammillothalamic tract, and just superior to the subthalamic nucleus [18]. With its relatively small size and medial location, the PTT is more amenable to MRgFUS lesioning compared to the globus pallidus interna, for example. Lesioning the PTT improves dystonia symptoms by interrupting the cortico-basal ganglia-thalamo-cortical circuit through the modulation of the pallidal efferents to the thalamus [17]. In 2019, radiofrequency PTT lesioning in 11 patients with dystonia resulted in significant improvement in their dystonia rating scores, as measured by the Burke-Fahn-Marsden Dystonia Rating Scale (BFMDRS) after a mean follow-up of 11.5 months [19]. In 2020, MRgFUS pallidothalamic tractotomy in 51 patients with chronic therapy-resistant PD, and with a median follow-up of 12 months, demonstrated significant improvements in dyskinesias, distal tremor, rigidity on the treated side, and other symptoms (e.g., distal hypobradykinesia, dystonia, pain), as well as a reduction in mean levodopa intake by 55% [20].

Recently, MRgFUS lesioning of the PTT was performed in Taiwan on four Filipino patients with genetically confirmed XDP [15, 16]. The XDP-Movement Disorder Society of the Philippines (XDP-MDSP) Scale [21] was used to assess their response, and the patients reported overall improvement ranging from 30–36% in their XDP-MDSP Scale score at 6 months and 1 year after the procedure [15, 16]. However, two patients reported arm pain 2–7 months post-treatment, most likely due to central pain syndrome [16].

The PGH is a national university hospital located in Manila, Philippines, catering to 600,000 service patients annually [22]. The cost of treatment for service patients undergoing surgery or other procedures is subsidized by the government insurance program, with no out-of-pocket expenditure for these patients. In 2020, the PGH acquired a MRgFUS system that is being used to treat patients with other movement disorders such as ET and PD. We would like to utilize the MRgFUS to perform pallidothalamic tractotomy on patients with XDP, building on the encouraging work that was started in Taiwan [15, 16]. XDP is a uniquely Filipino disease with very few effective treatment options, and we would like to investigate the efficacy and safety of MRgFUS in XDP.

The primary objective of this study is to estimate the efficacy of MRgFUS pallidothalamic tractotomy for treating dystonia and parkinsonism symptoms in patients with XDP.

## Methods

### Study design

This is a prospective study that aims to determine the improvement in the dystonia and parkinsonism of patients with XDP after MRgFUS pallidothalamic tractotomy (unilateral and staged bilateral). This study protocol was developed in compliance with the Standard Protocol Items: Recommendations for Interventional Trials (SPIRIT) 2013 checklist (see supplementary material 1).

### Setting and participants

The study will be conducted at the PGH, Manila, Philippines. Adult XDP patients aged between 18–65 will be recruited for this study. All participants will undergo MRgFUS pallidothalamic tractotomy. Based on the list of patients as of December 2022, there are approximately 30 XDP patients who have sought consult at the PGH within the past 4 years.

### Inclusion criteria

The inclusion criteria include: (a) aged between 18 and 65 years; (b) diagnosed with XDP confirmed by genetic testing, (c) skull density ratio (SDR) of ≥ 0.35 as determined by computed tomography, (d) psychiatric (anxiety and depression) clearance, (e) medical/cardio-pulmonary clearance, and (f) no severe dementia as assessed on a full neurocognitive test using the Wechsler Adult Intelligence Scale (4th edition), Wide Range Assessment of Memory and Learning (2nd edition), Wechsler Memory Scale (logical memory subtest), Boston Naming Test (2nd edition), Controlled Oral Word Reading Test, Wisconsin Card Sorting Test, Delis-Kaplan Executive Function System and the Hamilton Depression Rating Scale, to measure general intellectual function, episodic memory, language, attention and executive function, and affect [23]. Participants that may have undergone prior unilateral MRgFUS pallidothalamic tractotomy will also be eligible.

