The patients will be assessed within 24 hours of treatment then asked to follow up with the movement disorder neurologist ([name]) at 2 weeks, 3 months, 6 months, 9 months, and 12 months post-treatment through a clinic visit. A written and standardized video protocol for the movement exam will be presented to all participants which will show the rating scales such as XDP-MDSP Scale, BFMDRS, and Movement Disorder Society-Unified Parkinson’s disease Rating Scale (MDS-UPDRS). Video recording will be taken at the initial visit and at each of the follow-up visits. Another blinded assessor, who is not connected with the PGH, will be asked to score the videos of the patients. The primary outcome will be assessed using the XDP-MDSP Scale, BFMDRS, and MDS-UPDRS at each visit, which will then be compared to the pre-treatment baseline recordings. In addition, XDP clinical and functional stage will be assessed [1]. Adverse effects, including skin burn, headache, arm or leg pain, muscle weakness, paresthesia, and unsteady gait, will be monitored at every follow-up.

For patients who have previously undergone a unilateral MRgFUS pallidothalamic tractotomy, the contralateral lesion will be performed at 12 months following the first procedure, provided that there are no serious adverse effects from the first PTT lesioning.

Moreover, we will also look into the: (a) demographic and clinical profile, (b) neuroimaging findings (cranial computed tomography and MRI), (c) MRgFUS treatment parameters (number of sonications, maximum energy, maximum temperature, duration of treatment), (d) change in the non-motor features using the XDP-MDSP Scale, (e) change in the XDP clinical and functional stage, (f) change in the BFMDRS and the part III of the MDS-UPDRS, (g) to determine the improvement in the patient’s quality of life using the five-level EuroQol five-dimensional questionnaire (EQ-5D-5L) at baseline, 3 months, 6 months, 9 months, and 12 months, (h) Montreal Cognitive Assessment (MoCA) (English, Pilipino, or Hiligaynon versions) at baseline, 6 months, and 12 months, and (i) to determine the safety of unilateral and staged bilateral MRgFUS procedure (see supplementary material 2).

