### Data analysis plan

Descriptive statistics (mean, median, mode) of the numerical and nominal data will be obtained. Parametric tests will be used when our data follow normal distribution, otherwise, nonparametric test (Kruskal-Wallis test) will be used to compare the groups. The means of the 2 observer-masked scores pre-operative, 2 weeks, 3 months, 6 months, 9 months, and 12 months will be compared using a one-way analysis of covariance. A paired t-test will be done for the secondary endpoints: MoCA, EQ-5D-5L, and the nonmotor portion of the XDP-MDSP Scale. P-values of < 0.05 will be considered statistically significant. An interim analysis will be performed at either the 6-month timepoint or when 50% of patients have been enrolled, whichever comes first.

Protocol registration and technical review approval

This protocol was registered in the ClinicalTrials.gov website (Trial registration number: NCT05592028). It has received technical review board approval from the Department of Neurosciences, College of Medicine and Philippine General Hospital, University of the Philippines Manila.

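### Untreated and previously lesioned patients share one before-after comparison against a baseline that does not say which lesion it precedes

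*Protocol article*

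**What the plan says.** All places are in the Methods of the protocol article.

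- **Inclusion criteria:** "Participants that may have undergone prior unilateral MRgFUS pallidothalamic tractotomy will also be eligible". No limit on their number is given.
- **Study design:** one aim covers both unilateral and staged bilateral tractotomy.
- **Study procedure, staging:** "For patients who have previously undergone a unilateral MRgFUS pallidothalamic tractotomy", it states that "the contralateral lesion will be performed at 12 months following the first procedure", on condition that the first lesion caused no serious adverse effects.
- **Study procedure, visits and baseline:** after assessment within 24 hours, patients are seen "at 2 weeks, 3 months, 6 months, 9 months, and 12 months post-treatment through a clinic visit". The primary outcome scales are scored at each visit, "which will then be compared to the pre-treatment baseline recordings".
- **Data analysis plan:** the mean masked scores from the pre-operative visit to month 12 "will be compared using a one-way analysis of covariance". A Kruskal-Wallis fallback is to compare groups that are not defined.
- **Study procedure, item (i):** unilateral and staged bilateral treatment are named separately for safety, and nowhere else among the outcomes.

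**The concern.** Each element is ordinary on its own. The difficulty is how they combine. A first-time patient's change from baseline estimates the effect of a first lesion. In a patient already lesioned on one side, a score taken before the study procedure already contains the first lesion's effect, so the change shows only what the second side adds. If the baseline is instead the recording made before the first lesion, the change is cumulative over both sides. One overall mean over these patients estimates neither the unilateral nor the staged bilateral effect, and it moves with whatever mix of patients happens to enrol.

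The staging condition adds selection. Patients reach a second side only if the first went without serious harm, so their results do not carry over to first-time patients, for efficacy or for safety.

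At stake is the primary objective, which is to estimate efficacy. A reader counselling an untreated patient, or one considering the second side, needs the figure for that procedure.

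**Working it through.** The plan gives no figure on this point to reproduce. Table 1 of the Sample size section supplies only the lower total of 28 used in step 3; the argument does not depend on how that total was derived.

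**1. What the change measures for each kind of patient**

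Let D1 be the mean change after a first lesion in untreated patients, D2 the mean change recorded in previously lesioned patients, and q their share. The overall change is

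(1 − q) × D1 + q × D2.

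It equals D1 only if q = 0 or D2 = D1. The article gives neither q nor the baseline that fixes D2.

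**2. Illustration of size and direction**

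Inputs:
- Improvement of 30–36% on the XDP-MDSP Scale in four patients (Introduction). Laterality is not stated there, so treating this as a first-side effect is an assumption.
- Assumption: a second lesion removes the same percentage of the score present just before it.
- Assumption: q = 10%, 25% or 50%.

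With a score of 100 before any lesion:
- First-time patient: D1 = 30 to 36 points.
- Previously lesioned, baseline just before the second lesion: 70 × 0.30 = 21, and 64 × 0.36 = 23. D2/D1 = 21/30 = 0.70 and 23.04/36 = 0.64.
- Previously lesioned, baseline before the first lesion: 30 + 21 = 51, and 36 + 23 = 59. D2/D1 = 51/30 = 1.70 and 59.04/36 = 1.64.

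Pooled change relative to D1 is 1 − q + q × (D2/D1):

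| q (assumed) | Baseline before second lesion | Baseline before first lesion |
|---|---|---|
| 10% | 0.96–0.97 | 1.06–1.07 |
| 25% | 0.91–0.93 | 1.16–1.18 |
| 50% | 0.82–0.85 | 1.32–1.35 |

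Example: q = 25% with ratio 0.70 gives 0.75 + 0.25 × 0.70 = 0.925.

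The second-side effect is unknown, so a wider range is fair. If the second lesion added nothing, the pooled change on the pre-second-lesion baseline would be 1 − q: 0.90, 0.75 and 0.50. On the pre-first-lesion baseline it would be 1.00 throughout. The sign of the distortion thus depends on a definition that the article does not give.

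**3. Precision if the two sides are estimated separately**

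The 95% half-width for a mean change, in SD units, is t(0.975, n − 1)/√n. With N = 28 and an assumed 25% previously treated (21 and 7 patients):
- First side: 2.086/√21 = 0.46 SD
- Second side: 2.447/√7 = 0.92 SD
- Pooled: 2.052/√28 = 0.39 SD

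**The case against.** The strongest reply is that pooling is inferred, not stated. The Data analysis plan mentions groups without defining them, and unilateral versus staged bilateral is one possible meaning. Analysis sets and strata are also often left to a fuller document that is not shown. It stands that pooling is an inference. But the article itself states the eligibility rule, the baseline and the comparison, and the comparison as stated has nothing in it for prior lesion.

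Several stronger readings are tempting and are not supported:

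- **The second lesion falls on the 12-month endpoint.** The staging sentence concerns patients already treated once. If the first lesion came before enrolment, the contralateral lesion is their study treatment and does not meet their own month-12 visit. The two coincide only if both sides are treated within the study, and an assessment made just before the second lesion would then be unaffected. Month 12 is the last visit but is not singled out as the endpoint.
- **Bilaterally treated patients are counted twice.** No passage describes this.
- **Second-side safety is reported only with the whole group.** Item (i) of Study procedure names unilateral and staged bilateral safety.
- **The pooled mean understates the effect by a known amount.** Patient mix, second-side effect and baseline are all ungiven, and the direction can reverse.

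Restricting the primary analysis to untreated patients is also open to challenge. About 30 patients have consulted at the site in four years, and removing 7 of 28 leaves 21, below the lowest minimum of 24.5 in Table 1. That argues for modelling prior lesion rather than excluding these patients.

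**Conclusion.** The point holds in limited form. Followed as written, the plan yields a before-after change that combines a first-side effect with an added second-side or cumulative bilateral effect, the latter in patients selected by their tolerance of the first lesion.

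How large this is cannot be determined from the article. The multipliers in the working rest on an assumed share, an assumed equal percentage response and a four-patient range of unstated laterality. They show that the distortion can be small with few such patients and material with many, and that it can go either way. The defect lies in the definition of baseline and in the form of the primary comparison, and it can be corrected before analysis without losing patients.

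**What to change.** 1. Define baseline and time zero as immediately before each study procedure, and count visits from that procedure.
2. Put procedure (first or second side) by visit in the primary model, with patient as a random effect. Keep all patients in the model.
3. Report change and safety separately for first-side and second-side procedures, and state that second-side patients are those without serious adverse effects from the first lesion.
4. If both sides are treated within the study, state that the month-12 first-side assessment is recorded before the contralateral procedure.
5. Reconcile Inclusion criteria with Study procedure: the first sets no interval since a prior lesion, while the second fixes 12 months, which cannot be met by a patient lesioned longer ago. Whether and when a second lesion is done is a clinical matter and is not addressed here.

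The work is wording in the analysis plan and the order of assessment and procedure at one visit. The statistical cost is the wider intervals shown in step 3 of the working. The second-side estimate in particular would be descriptive if few such patients enrol.

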### Exclusion criteria

The exclusion criteria include: (a) patients with movement disorders other than XDP, (b) patients with abnormal neuroimaging findings that would preclude MRgFUS lesioning, (c) SDR < 0.35, (d) patients with metallic hardware (i.e., cochlear implants, brain stimulators or electrodes, aneurysm clips, cardiac pacemaker, implantable defibrillator), and (f) medical conditions such as a history of epilepsy, the presence of a brain lesion (vascular, traumatic, neoplastic, infectious, or metabolic), bleeding diathesis, open wounds in the head, and claustophobia. 

### Sample size

The sample size for this study was computed to range between 28 and 70 participants (see Table 1), with an expectation of a medium or large effect, using repeated measures Analysis of Variance (RM-ANOVA) for within-subject comparisons (as measures are taken 3 times per patient). To compute for the sample, the wp.rmanova function from WebPower package was used [24].

**Table 1 Tab1:** Sample Size Computations

F value	Minimum Sample (n*)	Inflated Sample Formula: n* / (1-DOR)
0.25 (Medium Effect)	62.5	69.5
0.30	43.5	48.5
0.35	32.5	36
0.40 (Large Effect)	24.5	27.5

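### Table 1 gives half-patients that do not reproduce as totals for the single treated cohort, so the 28 to 70 range needs recalculating as one whole-number target

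*Protocol article*

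**What the plan says.** The Sample size section of the protocol article bases the number on a calculation "using repeated measures Analysis of Variance (RM-ANOVA) for within-subject comparisons", with the reason that "as measures are taken 3 times per patient". It adds that "the wp.rmanova function from WebPower package was used". Table 1 gives, for f = 0.25, 0.30, 0.35 and 0.40:

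- minimum sample: 62.5, 43.5, 32.5, 24.5
- sample inflated for dropout: 69.5, 48.5, 36, 27.5

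The outer inflated entries, rounded up, become the study figure: "The sample size for this study was computed to range between 28 and 70 participants". No alpha, power or dropout rate is given for the calculation.

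Other sections bear on this:

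- **Setting and participants:** every participant receives the procedure, and "there are approximately 30 XDP patients who have sought consult at the PGH within the past 4 years".
- **Study procedure:** follow-up takes place "at 2 weeks, 3 months, 6 months, 9 months, and 12 months post-treatment through a clinic visit".
- **Data analysis plan:** scores are compared across the pre-operative assessment and those five visits, significance is P < 0.05, and an interim analysis is triggered at 6 months or at half of enrolment, whichever is earlier.

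**The concern.** A sample-size calculation for one cohort should end in whole patients. All four minimums end in .5, and doubled they are 125, 87, 65 and 49. That pattern suggests a total divided by two, yet the article reports the result as the size of the whole study. If the entries are halves, the study is about half the size its own calculation requires, and the statement that it is sized for a medium or large effect fails.

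Two further problems do not depend on where the halves came from. The calculation assumes 3 measurements where the analysis uses 6. And a range is not a target: half of enrolment is 14 if the target is 28 and 35 if it is 70, so the interim trigger is not fixed, and recruitment could be declared complete at any number in between.

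**Working it through.** **Inputs from the article.** f = 0.25, 0.30, 0.35, 0.40; 3 measurements; one treated cohort; alpha 0.05 from the Data analysis plan.

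**Assumptions.** Dropout of about 10%, from the ratio of the two columns (62.5/69.5 = 0.90; 24.5/27.5 = 0.89). Sphericity. Noncentrality n × f², taken as the convention of the named function, whose source is not among the documents.

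**Formula.** Power = P(F′ > F critical), where F′ is noncentral F with df1 = 2, df2 = 2(n − 1) and λ = n × f². Solve for n.

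**Step 1: Table 1 read as totals.** No row reproduces:

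| f | Table minimum | n, alpha 0.10, 80% | n, alpha 0.05, 70% | n, alpha 0.05, 80% |
|---|---|---|---|---|
| 0.25 | 62.5 | 124.53 | 124.73 | 155.66 |
| 0.30 | 43.5 | 86.83 | 87.08 | 108.56 |
| 0.35 | 32.5 | 64.11 | 64.38 | 80.16 |
| 0.40 | 24.5 | 49.36 | 49.65 | 61.73 |

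**Step 2: Table 1 read as half-totals.**

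- *Alpha 0.10, 80% power.* n/0.9 = 138.36, 96.48, 71.23, 54.84. Rounded up: 139, 97, 72, 55. Halved: 69.5, 48.5, 36, 27.5, which are all four inflated entries. For the minimums, n rounded up and halved is 62.5, 43.5, 32.5, 25.0, which matches three of four (the table has 24.5).
- *Alpha 0.05, 70% power.* n/0.9 = 138.59, 96.76, 71.53, 55.16. Rounded to nearest and halved, these give the same four inflated entries. Rounded up, the last becomes 56/2 = 28.0, not 27.5. The minimums, rounded up and halved, are 62.5, 44, 32.5, 25, which match two of four.
- *Alpha 0.05, 80% power.* Half of n rounded up is 78, 54.5, 40.5, 31, which matches none.

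**Step 3: power at Table 1's minimums on this convention.** At alpha 0.05: 0.398, 0.395, 0.397, 0.386. At alpha 0.10: 0.527, 0.525, 0.527, 0.517.

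**Step 4: the other common convention, λ = 3 × n × f²/(1 − ρ), alpha 0.05.** Power at the table's minimums is 0.867, 0.864, 0.865, 0.853 at ρ = 0, and higher for positive ρ. At 80% power and ρ = 0 the required n is 52.9, 37.2, 27.7, 21.6, and it falls as ρ rises, so Table 1 is not recovered. The nearest setting found was 90% power with ρ = 0.1: 62.25, 43.70, 32.52, 25.26. That is close in three rows, but in whole patients it is 63, 44, 33, 26. It misses the last row and does not explain entries ending in .5.

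**Step 5: interim trigger and pool.** 28/2 = 14 and 70/2 = 35. Against about 30 known patients, 28 is 28/30 = 93%, and the other three inflated sizes exceed 30.

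**Step 6: what 28 enrolled would give.** 28 × 0.9 = 25.2, so about 25 evaluable. For a single-group change, the 95% CI half-width is t(0.975, 24)/√25 = 2.064/5 = 0.41 SD of the change. A two-sided paired t-test at alpha 0.05 has 80% power for a standardised mean change of 0.58.

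**The case against.** The strongest reply is that the article states no alpha, power or dropout rate, so any account of how Table 1 arose is reconstruction, and the power figures depend on how the software defines f. That stands. A reader might infer that the trial was sized at 70% power, or that its power is 39-40% as a fact. The documents support neither. Alpha 0.10 with 80% power fits slightly better than alpha 0.05 with 70%, and under the other convention the same numbers would be adequate.

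A second reply is that the halves may be per-group numbers. The article describes unilateral and staged bilateral treatment, admits patients with a prior unilateral lesion, and speaks of comparing groups. So it cannot be said that the authors mistook a one-group trial for a two-group one. But nothing labels Table 1 as per group, and if it is, 28 to 70 is still not the study total.

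Third, a reader might conclude that recruiting more than 30 is impossible. The article does not show that: the figure is a past count of consultations at one hospital, while enrolment runs from 2023 to 2026 and new patients may come forward.

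Finally, a journal article may leave calculation inputs to the full protocol. Their absence is therefore not the point. The printed numbers are.

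**Conclusion.** The point holds and should be corrected before the sample size is relied on. Three parts need no assumption about the software: the entries are half-patients, the calculation uses 3 measurements where 6 time points are analysed, and the study figure is a range that leaves the interim trigger between 14 and 35.

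The size of the shortfall is conditional. If λ = n × f², the unhalved totals are about 125, 87, 65 and 50 (139, 97, 72 and 55 after about 10% dropout), so the range would be 55 to 139. At alpha 0.05 and 80% power they are 156, 109, 81 and 62 before dropout. Power at the printed minimums is then about 39-40% at alpha 0.05, or 52-53% at alpha 0.10. If alpha 0.10 was in fact used, it conflicts with the P < 0.05 of the Data analysis plan. Under the other convention power would be 85% or more, but no setting tried there gives the table's entries. The pool of about 30 is a feasibility caution and not a cap.

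**What to change.** - Replace Table 1 with whole-number totals from a calculation that matches the design: one cohort (or groups that are named), the number of time points actually analysed, and alpha 0.05. Print the power, dropout rate, correlation assumption and definition of f beside it.
- Name one target N and define the interim trigger as a number of patients.
- State what that N delivers. If it is 28 with about 25 evaluable, the Step 6 figures could be quoted. The paired change at month 12 is only an illustration of such a statement; it suits the stated aim of estimating efficacy, but the authors should use the comparison they intend as primary.
- Reconcile the chosen N with the roughly 30 patients seen in 4 years.

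The cost is a text and table correction and a less favourable stated figure. No extra patients are needed.

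### The 28 to 70 range is sized on three measurements per patient, but the plan measures and compares the primary scales at six time points, so the range was not derived for that comparison

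*Protocol article*

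**What the plan says.** All references are to the protocol article.

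- **Sample size.** The calculation was made "using repeated measures Analysis of Variance (RM-ANOVA) for within-subject comparisons", and the bracket that follows gives the reason: "as measures are taken 3 times per patient". For software, "the wp.rmanova function from WebPower package was used". Table 1 runs from f = 0.25 (minimum n 62.5, inflated 69.5) to f = 0.40 (24.5, inflated 27.5), which the text rounds to 70 and 28.
- **Study procedure.** After an assessment within 24 hours, patients are seen at "2 weeks, 3 months, 6 months, 9 months, and 12 months post-treatment through a clinic visit". The XDP-MDSP Scale, BFMDRS and MDS-UPDRS carry the primary outcome. They are rated at each visit and set against the pre-treatment recordings.
- **Data analysis plan.** The observer-masked scores "pre-operative, 2 weeks, 3 months, 6 months, 9 months, and 12 months will be compared". That is six occasions.
- **Other outcomes.** The MoCA is taken "at baseline, 6 months, and 12 months". The EQ-5D-5L is taken five times (baseline, 3, 6, 9 and 12 months). The Data analysis plan lists both as secondary endpoints.

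**The concern.** The number of occasions is an input to a repeated-measures calculation. It sets the degrees of freedom of an overall within-subject test: 3 - 1 = 2 in the numerator for three occasions, 6 - 1 = 5 for six. Depending on how the effect size is defined, it also enters the non-centrality. A range computed for three occasions is therefore not the range for six.

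Two things are at stake. A reader cannot tell what power or detectable effect the trial has for the comparison it describes. Nor can a reader tell which three visits the sizing had in mind, and so which visits the efficacy conclusion is meant to rest on. The Setting and participants section counts about 30 XDP patients seen at the hospital over the past four years, so recruitment may well end near the bottom of the range, where a correct statement of power matters most.

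**Working it through.** **Step 1. Count the occasions.**

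| Section | What is counted | Occasions |
|---|---|---|
| Sample size | Measures per patient | 3 |
| Study procedure | Primary scales: baseline plus five clinic visits | 6 (7 if the 24-hour assessment is rated on the scales) |
| Data analysis plan | Time points compared | 6 |
| Study procedure | EQ-5D-5L (secondary) | 5 |
| Study procedure | MoCA (secondary) | 3 |

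No primary outcome follows a three-occasion schedule. This step settles the point; the rest asks how much it matters.

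**Step 2. Inputs for a recalculation.**
- From the article: m = 3 occasions; f = 0.25, 0.30, 0.35, 0.40; alpha 0.05 (given for the analysis, not repeated for the sizing).
- Dropout: no rate is given, but the ratio of the two columns in Table 1 implies about 10% (1 - 62.5/69.5 = 10.1%; the four rows give 9.7% to 10.9%).
- Not given: power, sphericity correction, correlation between occasions, number of groups, effect-size convention. Assumed here: 80% power, sphericity, one group.

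**Step 3. Try to reproduce Table 1.** Solve for n in a non-central F test with df1 = m - 1 and df2 = (n - 1)(m - 1), under two conventions for the non-centrality:
- A: lambda = n x f²
- B: lambda = n x m x f², occasions uncorrelated

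| f | Table 1 minimum n | A, m = 3 | B, m = 3 |
|---|---|---|---|
| 0.25 | 62.5 | 155.7 | 52.9 |
| 0.30 | 43.5 | 108.6 | 37.2 |
| 0.35 | 32.5 | 80.2 | 27.7 |
| 0.40 | 24.5 | 61.7 | 21.6 |

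Neither reproduces the table at 80% power. Under A the stated minimum n gives only about 39% to 40% power with three occasions. All four rows can be matched under A if the result is halved and power is set to 70% (62.4, 43.5, 32.2, 24.8). The article states neither step, and other unusual input sets fit about as well, so this match shows nothing about what was actually done.

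**Step 4. Change only the number of occasions, from 3 to 6.**

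| f | A: m = 3 to m = 6 | Ratio | B: m = 3 to m = 6 | Ratio |
|---|---|---|---|---|
| 0.25 | 155.7 to 206.4 | 1.33 | 52.9 to 35.3 | 0.67 |
| 0.30 | 108.6 to 143.6 | 1.32 | 37.2 to 24.9 | 0.67 |
| 0.35 | 80.2 to 105.8 | 1.32 | 27.7 to 18.6 | 0.67 |
| 0.40 | 61.7 to 81.3 | 1.32 | 21.6 to 14.5 | 0.67 |

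Take the n that gives 80% power with three occasions and test six instead. Power becomes about 66% under A and about 95% under B.

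Under A, lambda depends on n and f alone, so the extra degrees of freedom dilute a fixed signal. Under B, each added occasion adds to lambda and outweighs the extra degrees of freedom. The sign of the change turns on a convention that the article does not state.

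**The case against.** **A reader might infer that the trial is underpowered.** The documents do not support that. It follows only if the non-centrality is n x f² with f held fixed as the occasions double. Under the other convention the same change raises power. The calculation that gives the 66% figure also starts from sample sizes about 2.5 times those in Table 1 (155.7/62.5 = 2.5), so it describes a hypothetical sample and not this trial's.

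**The overall test over six occasions is itself an inference.** The Data analysis plan names a one-way analysis of covariance, and the Study procedure section speaks of comparison with the pre-treatment recordings, which could mean separate contrasts of each visit with baseline. If so, a 5-degree-of-freedom test is not the primary test and the figures in Step 4 do not apply to it. This objection stands against the size of the effect. It does not rescue the sizing: under this reading, too, the plan's comparison is not a three-occasion repeated-measures test.

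**Could the three be the three rating scales, or the MoCA visits?** The bracket says how many times measures are taken per patient and offers this as the reason for a within-subject design, so it does not mean three scales. The MoCA has three visits, but nothing ties the sizing to it and it is secondary.

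**Could a fuller protocol or a separate analysis plan settle it?** It might name three primary occasions. The point here, however, is not missing detail. The article states one number in the sizing and another in the schedule and analysis.

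**Conclusion.** The inconsistency is explicit and needs no assumption: three measurements per patient in the sizing, six in the schedule and the analysis, with no three designated as primary. The range of 28 to 70 was not derived for the comparison that the plan makes.

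The consequence for sample size is indeterminate. At an assumed 80% power, alpha 0.05, sphericity and one group, the required n for an overall within-subject test moves by about +32% or about -33% depending on the effect-size convention. These bounds illustrate sensitivity. They are not corrected sample sizes, since neither convention reproduces Table 1 at 80% power.

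The plan should be corrected on this point, but the finding gives no ground for saying that the trial needs more patients.

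**What to change.** Make the sizing and the comparison agree, by one of two routes:

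1. **Keep six occasions.** Replace three with six in the Sample size section, rerun the calculation, and restate the power or the detectable effect at the number of patients that can realistically be enrolled. State the inputs beside it: power, alpha, dropout rate, number of groups, sphericity correction, and how f is defined, including any correlation assumed between occasions.
2. **Keep three occasions.** Name in advance, in both the Sample size section and the Data analysis plan, the three that carry the primary comparison, and treat the other visits as descriptive. Which three is for the investigators to choose; the documents do not point to any. The same inputs should still be stated so that Table 1 can be reproduced.

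Either route is a change to two paragraphs and a short recalculation. Neither adds patients or visits. Under the first, the restated power or detectable effect may come out better or worse than the present range suggests. Under the second, the visits not named give up their confirmatory role.
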